## Abstract

**Introduction:**

The EQ-5D is a widely used health-related quality of life (HRQoL) instrument. The recall period “today” may miss out on recurrent health fluctuations often observed in people with dementia (PlwD). Thus, this study aims to assess the frequency of health fluctuations, affected HRQoL dimensions and the impact of the health fluctuations on the assessment of health today using the EQ-5D-5L.

**Methods and analysis:**

This mixed-methods study will base on n=50 patient and caregiver dyads and four main study phases: (1) Baseline assessment of patients' socio-demographic and clinical characteristics; (2) caregivers self-completion of a daily diary for 14 days, documenting patient's today's health compared to yesterday, the affected HRQoL dimensions, and events that could have caused the fluctuations; (3) administration of the EQ-5D-5L as self- and proxy-rating at baseline, day seven and day 14; (4) interviewing caregivers on patient's health fluctuation, the consideration of past fluctuations in the assessment of health today using the EQ-5D-5L, and the appropriateness of recall periods to capture health fluctuations on day 14. Qualitative semi-structured interview data will be analyzed thematically. Quantitative analyses will be used to describe the frequency and intensity of health fluctuations, affected dimensions, and the association between health fluctuation and its consideration in the assessment of health today.

**Discussion:**

This study aims to reveal insights into the health fluctuation in dementia, the affected dimensions, and underlying health events, as well as whether individuals adhere to the recall period of health today using the EQ-5D-5L. This study will also provide information about more appropriate recall periods that could better capture health fluctuations.

**Trial registration:**

This study is registered in the German Clinical Trials Register (DRKS00027956).

## Introduction

The EQ-5D-5L is a widely used preference-based generic instrument that measures today's self-rated health-related quality of life (HRQoL) (1). However, the health state can fluctuate from day to day in various chronic diseases such as Alzheimer's and other related dementia diseases (2, 3). People living with dementia (PlwD) and their caregivers often refer to this as “spells of good and bad days” (4). PlwD may have improved overall cognition, function, interest, and initiation on good days, while on bad days, there are frequent verbal repetition, poor memory, increased agitation, and other disruptive behaviors. Thus, clinically important symptom variability appears common in dementia (4). Cognitive and non-cognitive symptoms, such as anxiety, depression, pain, and discomfort can cause changes in the severity of symptoms and affect other health domains, including the patient's daily activities and self-care. Even though the EQ-5D-5L has proven acceptability, feasibility, and validity for moderately cognitively impaired PlwD, health state fluctuation in dementia might still significantly affect the assessment (5–7).

So far, challenges in measuring HRQoL and the impact of health state fluctuations have not been well-understood. Fluctuations of predominantly cognitive symptoms have been assessed clinically for Alzheimer's and Lewy body dementias (8). Sun et al. (2) showed an association of cognitive fluctuations with poorer HRQoL. However, health state fluctuations in HRQoL regarding PlwD has not been assessed yet. Blome et al. (9) showed that fluctuations in HRQoL frequently occur between and within days and impact the assessment of today's health with the EQ-5D-5L in patients with relapsing-remitting and secondary progressive multiple sclerosis. The authors recommended that a longer recall period or a mean of several measurements over a seven-day period should be used to capture important fluctuations of health states (9). Mitchell et al. highlighted among 30 patients requiring kidney care in individual semi-structured interviews with the “think-aloud” technique that when patients were asked to complete the EQ-5D-5L, more than one out of ten patients made errors and struggled to complete the questionnaire (10). This was mainly due to patients not understanding the instructions for the time window and the assessment phrase “your health today” of the EQ-5D-5L.

Thus, the lack of understanding of the questionnaire and its recall period might influence the assessment of the patient's actual HRQoL status, especially in those experiencing recurrent health fluctuations (11). Therefore, health state fluctuations could also unconsciously be included in the rating of the patient's present self-reported HRQoL or by proxy-reports by caregivers. Based on these considerations, the recall period of 1 day (today's health) might not capture recurrent health fluctuations. Even “today” may cause ambiguity. For example, “today” at 10 AM might differ from “today” at 10 PM for a patient's actual self-rated health. A longer recall period, especially for those HRQoL dimensions that are likely affected by health fluctuations, could have the potential to better capture health state fluctuations, resulting in a lover variability and higher reliability of the instruments values. However, evidence suggesting this hypothesis is lacking. Therefore, it is vital to understand health state fluctuation, the affected dimensions, and if recurrent health state fluctuations were considered in the assessment of today's health.

### Objective

This study aims to (i) quantify the occurrence, frequency and intensity of health state fluctuations and underlying health events over 14 days, (ii) identify which HRQoL dimensions may be affected by these fluctuations, and (iii) evaluate if past fluctuations are considered in the assessment of health today using the EQ-5D-5L. Furthermore, if the latter is true, this study aims (iv) to determine which recall period would be more appropriate to capture health state fluctuations in dementia.

## Methods and analysis

### Study design and setting

To understand and explore the impact of health state fluctuations in dementia on the EQ-5D-5L assessment of today's health, this study will be carried out as an explorative, single-group, observational study that combines quantitative and qualitative (mixed) methods over the following four main study phases (see Table 1): (I) Quantitative baseline assessment (socio-demographics and clinical data) from both PlwD and family caregivers *via* interview at patients and caregivers home, (II) daily completion of the paper-pencil diary by the caregiver over 14 days, and (III) quantitative follow-up assessment *via* interview and (IV) qualitative semi-structured interviews at patients and caregivers homes after the 14 day assessment period.

**Table 1 T1:** Questions of the semi-structured interview.

**#**	**Question**
1	“Were you able to complete the diary every day?”.
2	“How easy or difficult was it for you to answer the diary? Why?”
3	“Were there any fluctuations in your relative's condition? What were the fluctuations?”
4	“Were the last 2 weeks typical of his/her normal situation?”
5	“What events did you note positively in the diary? What events did you note negatively in the diary? Why?”
6	“Are the events frequent? Can you describe how often they occur?”
7	“How exactly is your relative's condition affected? What areas of health were frequently affected?”
8	“Can you describe how important this area is to your relative's health?”
9	“Do you think your relative is aware of these fluctuations?”
10	“Now that we have discussed the diary entries, I want to talk about the 5-question questionnaire (EQ-5D-5L) you completed. Is the questionnaire a good reflection of the state of your health?”
11	“How easy or difficult was it for you to answer the questionnaire?”
12	“Are some questions more difficult than others? If so, why?”
13	“In the questionnaire, you are asked to describe your relative's CURRENT state of health. On all 3 days, did you only consider your relative's current state of health? Or did you include a longer time (yesterday or last week) when answering the questionnaire?”
14	“Thinking about the last 14 days, do you think your relative's health today is a good reference for their general health?”
15	“Do you have a suggestion for an alternative time of demand?”
16	“How often do you think this questionnaire (EQ-5D-5L) should be administered to better represent your relative's health?”
17	“Do you think your relative would have answered these questions differently? If yes, why?”

After an initial socio-demographic and clinical baseline assessments of PlwD and their caregivers *via* interview at home, the caregiver will be instructed to complete a daily health diary (paper-pencil) for 14 days, documenting the PlwD's health state fluctuations, their intensity, HRQoL domains affected, and health events that could have caused the health fluctuation. HRQoL will be assessed *via* an interview using the EQ-5D-5L as self- and proxy-rating (proxy-proxy) at baseline, day seven and 14. Subsequently, the caregiver will be interviewed about the documented health state fluctuation, whether these fluctuations were considered in the assessment of the patient's today's health using the EQ-5D-5L, and (if the latter is true) what recall period would be more appropriate to capture health fluctuations in dementia.

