### Data collection

At baseline, day seven and day 14, the EQ-5D-5L (13, 14) will be administered *via* standardized face-to-face interviews by dementia-specific qualified nurses at patients' or caregivers' homes. Both patients (self-rating) and caregivers (proxy-rating) will be asked to complete the EQ-5D-5L (in separate rooms). Also, patients' socio-demographic (age, sex, living situation) and the following clinical data will be assessed at baseline: cognitive impairment according to the Mini-Mental State Examination (MMSE) (15, 16), depression according to the Geriatric Depression Scale (17), perceived social support according to the F-SozU (18), deficits in daily living activities according to the Bayer Activities of Daily Living Scale (19), and comorbidity according to the Charlson Comorbidity Index (20, 21). A brief description of the assessed clinical outcome measures is demonstrated in the section “measures.”

After completing the baseline assessment, caregivers will daily self-complete a fluctuation diary for 14 days, documenting the frequency and intensity of health state fluctuations, affected dimensions, and underlying health events (see Figure 2). After completing the fluctuation diary, the diary data will be collected, and the study nurse will conduct a semi-structured interview on day 14 about the documented recurrent health state fluctuations, the possible consideration of these fluctuations in the assessment of health today using the EQ-5D-5L, and appropriate recall periods to capture recurrent fluctuations of HRQoL more accurately in dementia. The questions of the semi-structured interview are displayed in Table 1. Furthermore, guidelines will be drafted, and the nurses will be trained to ensure the replicability of interviews and promote data quality.

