i. To assess the frequency and intensity of the health state fluctuation, caregivers document if patients' today's health is much (+2) or somewhat better today (+1), about the same (±0) today, or somewhat (−1) or much (−2) worse today compared to the day before. Also, a repeated administration of the EQ-5D-5L will also assess the health state fluctuation as a self- and proxy-rating at baseline (before starting the diary), seven days after starting the diary, and on the last day of the diary (day 14). The change in the EQ-5D-5L utilities, EQ-5D-5L level scores and level sum scores (LLS), and EQ-VAS scores from day 1 to day 7 and day 7 to day 14 can be used to assess the variability and reliability of each measure.ii. To assign health state fluctuations to specific health dimensions, we will use the health dimension of the diary and the assessment of EQ-5D-5L dimensions at baseline, seven, and 14 days. The caregiver will be instructed to document in the diary which dimensions could be assigned to the fluctuation of today's health state compared to the day before. We will use dimensions of the EQ-5D-5L and two other patient-reported outcomes measures (PROMs), the EQ Health and Wellbeing instrument (EQ-HWB) (22) and the dementia-specific Quality of Life–Alzheimer's Disease (QoL-AD) (23). The EQ-HWB has been designed as a standardized measure of aspects of health and well-being and has 25 items (24). In comparison, the QoL-AD is a widely used measure of the quality of life in dementia diseases that contains 13 items evaluating the domains of interpersonal relationships, financial difficulties, physical condition, memory, mood and overall health. Furthermore, caregivers could specify any other affected dimensions not listed in the diary. All dimensions are shown in Figure 2.iii. Caregivers will also be asked to document any health events that could have caused the health state fluctuations.iv. To evaluate the consideration of past health state fluctuations in the assessment of today's health, the EQ-5D-5L will be administered on day 14. Subsequently, the caregivers will be interviewed and asked whether or not recurrent health state fluctuations (if applicable) were considered in the assessment of health today using the EQ-5D-5L administered minutes before starting the interview. Furthermore, the caregiver will be asked to state what recall period would be more appropriate to assess HRQoL in people living with dementia more accurately.

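### Interview question 10 asks caregivers about their own health, although their EQ-5D-5L is a proxy rating of the patient, so its answers are open to mixed interpretation

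*Protocol article*

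**What the plan says.** The protocol article, under Study design and setting, identifies the interviewee: "Subsequently, the caregiver will be interviewed about the documented health state fluctuation". The section Outcome measures to assess health fluctuations repeats this for the day 14 visit: "Subsequently, the caregivers will be interviewed and asked whether or not recurrent health state fluctuations (if applicable) were considered in the assessment of health today".

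The EQ-5D-5L is given "using the EQ-5D-5L as self- and proxy-rating (proxy-proxy) at baseline, day seven and 14". The Data collection section assigns the two ratings: "Both patients (self-rating) and caregivers (proxy-rating) will be asked to complete the EQ-5D-5L (in separate rooms". The self-rating belongs to the patient and the proxy rating to the caregiver.

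Table 1 lists the 17 interview questions. Question 10 moves from the diary to the EQ-5D-5L with the words "I want to talk about the 5-question questionnaire (EQ-5D-5L) you completed", and then asks: "Is the questionnaire a good reflection of the state of your health". Three items later, question 13 says of the same form: "you are asked to describe your relative's CURRENT state of health".

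**The concern.** The person addressed as *you* in the interview is the caregiver. Taken literally, question 10 asks whether a form about the patient is a good picture of the caregiver's own health. That form was never meant to measure the caregiver's health.

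At stake is the one item that asks directly whether the EQ-5D-5L reflects the health of the person rated. The neighbouring items ask other things: questions 11 and 12 about difficulty, 13 and 15 about the time window, 14 about whether today stands for general health, and 16 about how often to administer the form. If some caregivers answer question 10 about themselves and others about the patient, the pooled answers have no single meaning. The article's own Limitations section warns that patients and caregivers perceive health differently, so whose health is meant needs to be clear in each item.

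The Data collection section promises guidelines and nurse training so that interviews can be replicated. With the item as printed, a nurse who reads it out passes on the ambiguity, and a nurse who corrects it on the spot departs from the guide.

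**Working it through.** No figure is involved, so the check sets the passages side by side.

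1. **Who is interviewed.** The caregiver, according to the Abstract, Study design and setting, and the outcome section. Nowhere is this interview given to patients.
2. **What the caregiver rated.** The patient, by proxy (Study design and setting; Data collection). Nowhere does the caregiver rate their own health on the EQ-5D-5L.
3. **Whose health each Table 1 item names.**

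| Question | Whose health or condition |
|---|---|
| 3, 4, 7, 8 | the relative's |
| 10 | the interviewee's |
| 13, 14, 16 | the relative's |

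Eight items specify whose health or condition is meant. Seven name the relative and 8 − 7 = 1, question 10, names the interviewee. Questions 9 and 17 also mention the relative, but about awareness of the fluctuations and how the relative would have answered.

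4. **Direct conflict.** Questions 10 and 13 concern the same completed form. Question 13 says that it describes the relative. Question 10, as worded, takes it to describe the person who filled it in. Given steps 1 and 2, only the wording of question 13 fits the design.

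5. **Reach.** One of 17 items (1/17, about 6%) carries the wording, and with the planned 50 dyads up to 50 caregivers hear it. This counts exposure to the wording, not wrong answers.

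6. **What depends on the item.** The primary outcomes rest on the diary, on changes in the EQ-5D-5L and EQ-VAS, on affected dimensions and events, and on whether past fluctuations entered the rating of today's health. Question 13 is the item that asks about that last point. The pre-set themes of the qualitative analysis are occurrence and frequency, intensity, affected dimensions, and recall period. Overall fit of the EQ-5D-5L is not among them. Question 10 therefore feeds none of the named outcomes or themes.

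**The case against.** The strongest reply is that context repairs the item. Question 10 opens by naming the form on which the caregiver has just rated the patient, and it follows seven questions about the relative or the diary (questions 3 to 9). The interview is semi-structured, so a trained nurse can clarify, and the article does not require verbatim reading. A pilot in five patients tests the measures before roll-out. The printed table may also be an English translation of a German guide that is worded correctly, although the article does not say so.

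Much of this stands, and it limits the claim. A reader might infer that every caregiver answers question 10 about the wrong person. The article does not support that: some will answer about the patient, and mixed interpretation is as far as the text goes. The reply does not make the printed wording right, however, and it leaves the meaning of each answer to the caregiver or the nurse. A possible translation slip is a reason to check the guide in use.

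A reader might also infer that the word CURRENT in question 13, where the instrument says today, lets caregivers who drew on earlier days count as adherent and so biases adherence upward. Question 13 itself answers this. It goes on to contrast the current state with a longer time and gives yesterday and last week as examples of the longer time, which points such caregivers to the second option. Any percentage for such a bias would need a true non-adherence rate and a misreading rate, and the article gives neither.

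**Conclusion.** The inconsistency is real and lies within the article: question 10 contradicts question 13 and the proxy design. Asked as printed, it yields answers that cannot be interpreted reliably as statements on whether the EQ-5D-5L reflects the patient's health.

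The impact is small and bounded. It is confined to this item. The primary outcomes stand, and so does the regression of adherence to the recall period, on the assumption that adherence is taken from question 13, the only item that asks about it. A reader might link question 10 to the Discussion's expectation of learning whether the five dimensions capture fluctuations. The Discussion does not make that link; it speaks of fluctuations and of variation in the EQ-5D-5L, not of the answers to this item.

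Two things remain unknown: whether the guide in use has the same wording as Table 1, and how many caregivers would answer about themselves. The correction is worth making because the wording is plainly wrong and the change costs almost nothing.

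**What to change.** - Reword question 10 so that it asks about the state of *your relative's* health, in line with question 13.
- Check the guide that the nurses use. If it already refers to the relative, only the published table needs correcting.
- For interviews already held with the printed wording, code from the transcript whose health each answer to question 10 concerns, and set aside answers about the caregiver's own health.
- Leave question 13 as it is.

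The cost is a change of a word or two, a short note to the nurses, and one extra code for existing transcripts. The downside is that earlier and later interviews will differ slightly on this one item, which should be stated when its answers are reported. The article does not say how many interviews have been held, so the amount of recoding cannot be given here.

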**Figure 2 F2:**
[figure not shown]
Health fluctuation diary (exemplary illustration for day 1).

On day seven of the self-completion of the 14-day diary, the nurse will visit the caregiver at their home and will glance over the caregiver's documentation from day 1 to day 7. The study nurse will provide further assistance, discuss inconsistencies in the documented answers and be available for any questions about completing the diary. This could avoid entry errors and missings and, therefore, promotes the retention of protocols. Furthermore, instructions will be provided on how to fill out the diary.

As an incentive for complete follow-up, the patient and caregiver receive a lump sum payment upon completion of the 14-day assessment period.

Before the study roll-out, a pilot study will be implemented for *n* = 5 patients, testing the acceptability, reliability and validity of the used measures. Data collection will take place between October 2021 and December 2022.

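### The adherence question asks for one answer on all three EQ-5D-5L ratings, although primary outcome (iv) is defined by the day-14 rating alone

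*Protocol article*

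**What the plan says.** Item (iv) of the section on outcome measures to assess health fluctuations ties the outcome to one rating: "To evaluate the consideration of past health state fluctuations in the assessment of today's health, the EQ-5D-5L will be administered on day 14". The caregiver is then asked whether recurrent fluctuations were considered in that assessment, "using the EQ-5D-5L administered minutes before starting the interview".

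Table 1 (Study design and setting) lists the interview questions. Question 13 asks "On all 3 days, did you only consider your relative's current state of health" and offers the alternative "Or did you include a longer time (yesterday or last week) when answering the questionnaire". The three days are the three EQ-5D-5L occasions: "at baseline (before starting the diary), seven days after starting the diary, and on the last day of the diary (day 14".

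Questions 1 to 9 cover the diary, the fluctuations and the events. Question 10 opens the questionnaire block with "Now that we have discussed the diary entries, I want to talk about the 5-question questionnaire (EQ-5D-5L) you completed".

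The section on quantitative data preparation and analyses makes adherence to the recall period, coded yes or no, the dependent variable. Fluctuation intensity in three classes is the main independent variable. The stated hypothesis is that more frequent and more intense diary fluctuations raise the odds of non-adherence.

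**The concern.** The described outcome concerns one rating made shortly before the interview. The printed question covers three ratings, the oldest made about two weeks earlier, before any diary entry existed. A caregiver who looked back only at baseline would answer that a longer time was included and could be coded as non-adherent, although no diary fluctuation could have influenced that rating. Likewise, fluctuations on diary days 8 to 14 could not have entered the day-7 rating, yet they count towards 14-day intensity.

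This affects a named primary outcome in two ways: the reported proportion of caregivers who depart from the recall period, and the regression of that variable on fluctuation intensity. Question 13 also asks about a longer time rather than about fluctuations, which moves it a little further from outcome (iv).

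**Working it through.** The document states no rate, alpha, power or effect size for this outcome, so there is no figure of the plan to reproduce. The check is a comparison of the text, followed by illustrations under stated assumptions.

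**Text comparison**

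| Item | Outcome measures, item (iv) | Table 1, question 13 |
|---|---|---|
| Ratings covered | 1 (day 14) | 3 (baseline, day 7, day 14) |
| Ratings made before the diary began | 0 | 1 of 3 |
| Age of the oldest rating when asked | minutes | about 14 days |
| Asked about | recurrent fluctuations | a longer time |

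Twelve questions precede question 13: nine on the diary, fluctuations and events (1 to 9) and three on the questionnaire (10 to 12). No other listed question asks whether the caregiver kept to the current state of health.

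**Effect on the proportion.** Let *p* be the probability of looking beyond today at one rating. Assume that *p* is the same on all occasions, that the ratings are independent, and that any look-back makes the pooled answer non-adherent. Then P(non-adherent) = 1 − (1 − *p*)³.

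- *p* = 10%: 1 − 0.9³ = 27.1%, about 14 of 50 dyads instead of 5
- *p* = 20%: 1 − 0.8³ = 48.8%, about 24 of 50 instead of 10
- *p* = 30%: 1 − 0.7³ = 65.7%, about 33 of 50 instead of 15

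If each caregiver behaves the same way on all occasions, the pooled proportion equals *p* and there is no inflation. Midway, with half of the caregivers fully consistent and half independent, *p* = 20% gives (20 + 48.8)/2 = 34.4%.

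**Effect on the association.** Assume day-14 non-adherence of 20% with low and 40% with high fluctuation. The odds ratio is (0.4/0.6)/(0.2/0.8) = 2.67.

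- *Day 14 pooled with a baseline rating whose look-back is unrelated to fluctuation.* At 10% baseline look-back: low 1 − 0.8 × 0.9 = 0.28, high 1 − 0.6 × 0.9 = 0.46, odds ratio 2.19. At 40%: 0.52 and 0.64, odds ratio 1.64. The association is diluted.
- *All three ratings pooled, day 7 behaving like day 14.* At 10% baseline look-back: low 1 − 0.8² × 0.9 = 0.424, high 1 − 0.6² × 0.9 = 0.676, odds ratio 2.83. At 30%: 0.552 and 0.748, odds ratio 2.41. The result lies on either side of 2.67.
- *Question order, with no true association (20% in both groups).* If a share *f* of adherent high-fluctuation caregivers reports a longer time because the diary has just been discussed, the high group shows 0.2 + 0.8*f*. For *f* = 10%, 20%, 30% this is 0.28, 0.36, 0.44, with odds ratios 1.56, 2.25, 3.14.

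Pooling can lower or slightly raise the odds ratio, and priming, if present, raises it. Nothing in the document sizes these effects against each other.

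**The case against.** The strongest reply is that the source of the dependent variable is inferred. The analysis section does not name question 13 and gives no coding rule. The interview is semi-structured, transcribed and coded by two researchers, and a nurse may probe day by day. The text after Table 1 also describes the interview without limiting it to day 14, which fits a broader reading. This stands in part: the document is inconsistent about scope, and question 13 is the source only because no other listed question could be. It does not resolve the conflict, since the printed wording requests one answer and item (iv) names one rating.

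A second reply is that looking back at baseline is non-adherence whether or not a diary existed. That is correct for adherence as such. It is not correct for outcome (iv), or for a hypothesis about fluctuations reported in the diary. A patient's earlier fluctuations may resemble those in the diary, so treating baseline look-back as unrelated to intensity is an assumption of the illustration.

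Three stronger readings are tempting, and the document does not support them.

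- A reader might infer that the design biases the result towards the stated hypothesis. That could follow from priming alone, which is inferred from the question order and not measured. Pooling can work the other way.
- A reader might infer that the diary discussion contaminates the day-14 rating. That rating precedes the interview, so the order can distort only the report about it. Questions 10 to 12 also intervene, and 14 days of diary keeping is itself a cue that reordering cannot remove.
- A reader might object that on day 7 the nurse "will glance over the caregiver's documentation from day 1 to day 7" with no order set relative to the EQ-5D-5L. A condensed article may leave visit order to the full protocol or the nurse guidelines, and the study-procedures figure is not shown.

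The present order also has a rationale: asking whether fluctuations were considered presupposes that they have been established.

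**Conclusion.** The mismatch stands on the document's own text. Outcome (iv) refers to one rating and question 13 to three, including one made before the diary. Followed as written, the guide yields an answer that cannot be assigned to day 14.

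The figures of 27%, 49% and 66% are upper bounds for equal per-rating rates of 10%, 20% and 30%, provided the same caregiver's ratings are independent or positively related and any look-back counts as non-adherent. Recall habits of one caregiver over two weeks are probably correlated, so the actual inflation is likely to be smaller, down to none. The direction of the net bias in the odds ratio is unknown. The wording should be corrected, because the correction is cheap and the variable serves a primary outcome. The finding does not show that the study's conclusion will be wrong.

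**What to change.** 1. Ask question 13 separately for each of the three ratings. Define the dependent variable of the regression from the day-14 answer, and say so in the analysis section. Keep the answers for baseline and day 7, and any overall answer, as qualitative information.
2. Preferably put the day-14 item directly after the day-14 EQ-5D-5L and before the diary is discussed, because the discussion may prime the report. This step is more debatable than the first. If the present order is kept so that fluctuations are established first, state the order as a limitation.
3. The Trial status section planned roll-out for February 2022 and the protocol version is dated 08-30-2022, so some dyads may already have been interviewed. For these, code the day-14 part from the transcript where it can be identified, flag the pooled wording, and run a sensitivity analysis without the answers that cannot be assigned to day 14.

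The cost is a slightly longer interview, a revised guide and a short nurse briefing. The real drawback is two versions of a key question within 50 dyads. The flag makes this visible but does not restore full comparability.
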